### Phase I: training of CHWs

A package of training materials was developed based on the existing literature and comments from the expert panel. The training program for the CHWs was examined in a previous feasibility study and shown to enhance participants’ knowledge of cancer, self-efficacy, and competence in working as CHWs [27]. The training of CHWs by the research team would require 14 h. Training will consist of seven sessions that cover the following: information about cervical cancer and screening; resources and access to screening tests; beliefs, myths, and misconceptions about cancer and cancer screening; barriers to cancer screening; facilitators and strategies to overcome such possible barriers; communication and problem-solving skills; and navigation support. The performance of the CHWs will be evaluated through an exit test. CHWs must obtain a pass in the exit test before they are considered eligible to deliver the CHW-led intervention.

### Phase II: implementation of the CHW-led intervention

#### Randomization and blinding

A cluster randomized trial is chosen because South Asian participants who are affiliated with the same center/association likely have close contact with one another through their attendance at the activities held at these centers or associations. Therefore, simple randomization will introduce a high risk of contamination because it can enable participants communicating the knowledge they have gained during the intervention with each other through their close contact, even though they are allocated to different arms.

Six centers and associations, located in districts with a large population of South Asians, have agreed to participate in this study. Each center or association will be randomized to one of the two arms: an intervention arm (*n* = 3) that will undergo immediate treatment (CHW-led multimedia intervention) or a wait-list control arm (*n* = 3) that will receive delayed treatment (the same CHW-led multimedia intervention, but provided after the intervention arm has completed the data collection). Each recruited CHW will be allocated to either arm according to the center or association she is affiliated with.

Research assistant 1 (RA1), who will help to recruit South Asian participants, will not know the subject allocation because recruitment is performed prior to randomization. A statistician, who is independent and blinded to the center/association and collection of data, will generate a random allocation sequence using a computer-generated randomization scheme. Participants from each center/association will be placed in their corresponding arm to avoid “contamination” across participants. Screening uptake and other secondary outcomes will be assessed by another research assistant (RA2) blinded to the arm allocation. CHWs will not be blinded because they are responsible for implementing the intervention. Figure 3 shows the study flow.

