### Subjects

#### Subjects for Phase I: CHWs

Six CHWs (two Indians, two Nepali, and two Pakistani) will be recruited from six different community centers or ethnic minority associations in Hong Kong. These CHWs will be nominated by the persons in charge of these centers or associations involved in cancer prevention and women’s health among South Asians. A panel of research team members including three professors, one research nurse, and one research assistant with a medical background will select the most appropriate nominees. The potential CHWs should meet the following six criteria: able to demonstrate an understanding of South Asian women’s health needs and sociocultural norms; fluency in English and Urdu/Nepali/Punjabi/Hindi; willing to participate in community outreach activities and provide health information, healthcare, and social services relevant to cancer prevention; willing to complete the CHW training program and meet its requirements; and willing to serve as CHWs.

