#### Subjects for Phase II: participants in the study

Prior to randomization, a trained research assistant (RA1) fluent in English and Urdu/Nepali/Punjabi/Hindi will approach potential subjects while they are attending various activities organized by the six participating community centers or ethnic minority associations. After an introductory presentation, women interested in participating in the study will be screened for eligibility. Inclusion criteria include: self-identified as South Asian (Pakistani, Indian, or Nepali); aged 25 years or older who have previously had sex; never had a Pap test or has not undertaken cancer screening in the past 5 years; have not been previously diagnosed with cancer; have not attended any intervention or education program related to cervical cancer screening in the previous year; and able to communicate in English, Urdu, Nepali, Punjabi, or Hindi and read English, Urdu, Nepali, or Punjabi.

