### Statistical analysis

Data will be double-entered for validation and checked for range before analyses. Data will be summarized and presented using appropriate descriptive statistics. The normality of continuous variables will be assessed using skewness and kurtosis statistics and a normal probability plot. Appropriate transformations, if needed, will be made on skewed variables before entering them into the inferential analysis. The baseline characteristics of the intervention and control arms will be compared by chi-square or independent *t* tests as appropriate. The effectiveness of the CHW intervention will be evaluated by comparing the proportions of subjects in both arms reporting cervical cancer screening uptake at T2 and the changes in level of readiness to take cancer screening at T1 and T2 with respect to T0 between the two arms. The statistical significance of these outcome comparisons will be evaluated using a permutation test, accounting for the potential design effect of the randomization conducted at a cluster level instead of for individual participants [30]. Specifically, differences in uptake rates and changes in the level of readiness will be computed for all possible combinations of arm assignments of the six ethnic minority associations, and the 2.5 and 97.5 percentiles of these differences will be set as the critical values for two-sided permutation tests for the corresponding outcomes. Statistical analyses will also be conducted using SAS release 9.4 (SAS Institute Inc., Cary, NC, USA). All statistical tests will be two-sided with a level of significance set at 0.05.

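### Nothing in the 3:3 allocation of six associations balances CHW ethnicity, so 12 of 20 draws are uneven and could cost precision; separately, the 20-allocation permutation test cannot work at 0.05

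*Protocol article*

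**What the plan says.** Under Subjects for Phase I, the protocol article states: "Six CHWs (two Indians, two Nepali, and two Pakistani) will be recruited from six different community centers or ethnic minority associations". Under Randomization and blinding, "Each center or association will be randomized to one of the two arms", three per arm, and "Each recruited CHW will be allocated to either arm according to the center or association she is affiliated with". The method is described only by saying that an independent statistician "will generate a random allocation sequence using a computer-generated randomization scheme". No stratification, matching or constraint by ethnicity is mentioned.

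Under Statistical analysis, differences in uptake and in readiness change "will be computed for all possible combinations of arm assignments of the six ethnic minority associations", and the 2.5 and 97.5 percentiles of these differences become the critical values of a two-sided test at 0.05. That reference set is the one for 3:3 allocation with no further restriction.

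Of the sites, the article says: "Six centers and associations, located in districts with a large population of South Asians, have agreed to participate in this study". It does not give the ethnic make-up of any association. Women of all three groups are eligible, and ethnic group is recorded for each participant.

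**The concern.** With three clusters per arm, one draw decides which associations, and which CHWs, stand on each side. The CHW gives the talks, makes the calls and helps with navigation, so her ethnicity is part of how the intervention is delivered. The design has exactly two CHWs per ethnicity, which would allow perfect balance, yet nothing in the stated allocation secures it. If the associations are also ethnically distinct and the groups differ in underlying uptake, an uneven draw would move the observed arm difference for reasons other than the intervention, and the planned comparison does not adjust for ethnicity.

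The test has a problem of its own. With only 20 possible assignments, it may be unable to deliver the significance level that the article sets.

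**Working it through.** **Inputs.** From Sample size: 37% against 60%, 15% attrition, ICC 0.021, 68 women per association. From Subjects for Phase I: two CHWs per ethnicity. Assumed, because the article gives no figures: the spread in uptake between ethnic groups, and the share q of an association's women who belong to its CHW's ethnic group.

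**The plan's own figures.** The standard two-proportion formula gives 73 per arm (pooled variance) or 70.2 (unpooled), against 72 stated. Attrition: 72/0.85 = 84.7, so 85. Cluster size: 170 × [1 + (m − 1) × 0.021] = 6m gives m = 166.43/2.43 = 68.49, against 68 stated. These agree closely enough to use. Women analysed per association: 68 × 0.85 = 57.8, about 58.

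**Allocations.** C(6,3) = 20. One association per CHW ethnicity in each arm: 2 × 2 × 2 = 8. The other 20 − 8 = 12 (60%) split 2–1–0 in one arm and 0–1–2 in the other. For CHW ethnicity this count needs no assumption.

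**From CHWs to women.** Let the remaining 1 − q of the women be divided evenly between the other two groups. In an uneven draw, each of the two separated groups differs between arms by q − 1/3 in its share: 67 points at q = 1, 47 at q = 0.8, 27 at q = 0.6 and 0 at q = 1/3. If underlying uptake differs by D between those two groups, the arm difference shifts by D × (q − 1/3), which is at most 2D/3.

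**How large a spread fits the plan.** The planned between-cluster variance is about 0.021 × 0.24 = 0.00504. Three equally spaced groups with a 20-point spread have variance (0.10² + 0 + 0.10²)/3 = 0.00667, which alone exceeds it. A 10-point spread has (0.05² + 0 + 0.05²)/3 = 0.00167, which fits and leaves 0.00337 for other cluster differences.

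**Precision, 10-point spread, q = 1.** Four draws separate the extreme groups (shift 2/3 × 10 = 6.7 points) and eight separate adjacent groups (2/3 × 5 = 3.3 points).

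- Variance from uneven draws: (4 × 0.0667² + 8 × 0.0333²)/20 = 0.00133.
- Remaining variance: (2/3) × (0.00337 + 0.24/58) = 0.00501.
- SD with no ethnic restriction: √(0.00501 + 0.00133) = 0.080. SD restricted: √0.00501 = 0.071.

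Simulation gives 0.081 and 0.070, with about 21% and 15% of estimates more than 10 points off. Power of the unadjusted cluster t-test is 58% either way.

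**Other spreads.** The table gives simulated power for a 23-point effect at q = 1. Here the spread is added on top of the 0.021, so these cases exceed the planned ICC as soon as the spread is above zero.

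| Spread | No ethnic restriction, unadjusted (4 df) | Restricted, unadjusted (4 df) | Restricted, adjusted (2 df) |
|---|---|---|---|
| 0 | about 60% | about 60% | about 37% |
| 10 points | 52% | 52% | 38% |
| 20 points | 35–36% | 30% | 38% |
| 30 points | 21–23% | 11% | 39% |

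After restriction, the unadjusted test has a type I error of about 1% at a 20-point spread and 0.1% at 30, so it is conservative there.

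**The permutation test.** Every assignment has a mirror image with the opposite sign, so the smallest two-sided p is 2/20 = 0.10. A 2.5% tail of 20 values holds 20 × 0.025 = 0.5 of a value. Depending on how the percentile is computed and whether ties count, either no result is ever significant, or the extreme pair is and the true level is 0.10. With 8 allocations the minimum would be 2/8 = 0.25.

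**The case against.** The article gives the ethnicity of CHWs, not of associations or women. A reader might infer that 12 of 20 draws confine two ethnic groups of women to one arm each. That would need every association to serve one group only, which is nowhere stated; with mixed membership the imbalance is partial or absent. This part of the objection stands, and every consequence for the women is conditional on it.

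A reader might also infer bias. The documents do not support that. The 20 assignments are equally likely, the estimate is right on average over them, and a permutation test already counts the uneven ones. What is lost is precision and a clean reading of the one draw that occurs.

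Nor would later adjustment be useless. An ethnicity-adjusted model can be fitted in all 20 draws and held its 5% error rate in simulation. It is costly, though: power is about 25% without restriction, against 38% with it.

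Large shifts, such as 13 points from a 20-point spread, rest on a spread that exceeds the plan's own ICC. The gain consistent with the plan is the modest one at 10 points.

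Finally, restriction is not free. It leaves 8 allocations, and adjustment costs about 14 to 23 points of power when groups differ by 10 points or less. The shrinkage to 8 forfeits no attainable significance, because 20 allocations cannot reach 0.05 either, but that reply holds only if the test is replaced as well.

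**Conclusion.** The concern holds in a limited form. As described, allocation is 3:3 with no ethnic restriction; this rests on the silence in Randomization and blinding together with the reference set in Statistical analysis. On that reading, 60% of draws leave CHW ethnicity uneven between arms. Whether the women's ethnicity follows depends on an unstated feature of the associations. If it does, with a 10-point spread inside the planned ICC, restriction cuts the SD of the estimate by about one eighth and the chance of an error above 10 points by about 6 percentage points. In the scenarios simulated it never materially worsened precision. It does not raise power at that spread.

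The defect in the test is firmer and needs no assumption about ethnicity: a two-sided permutation test over 20 assignments cannot operate at 0.05.

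**What to change.** **Statistical analysis.** Before outcomes are compared by arm, replace the permutation test with a two-sample t-test on the six association proportions (4 df), and use association means for the readiness changes. This needs no extra women or sites. It relies on roughly normal cluster summaries, and its power under the plan's inputs is about 60%, below the planned 80%; that should be stated.

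**Randomization and blinding, if allocation is still open.** Randomise one of the two associations of each CHW ethnicity to each arm, and pre-specify whether ethnicity enters the analysis. This is one instruction to the independent statistician. The price is 8 rather than 20 allocations, 2 df if adjusted (power about 37% against 60% when groups do not differ), and a conservative unadjusted test if groups differ by 20 points or more.

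**If allocation is already done**, which is likely because Trial status gives a start on 1 September 2018: report the scheme actually used, tabulate the already collected ethnic group by arm and association, and limit the causal claim if a group proves to be confined to one arm. If the scheme was in fact restricted, the set of all assignments is the wrong reference set and the text must be corrected.

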**Fig. 3 Fig3:**
[figure not shown]
Flow diagram of the intervention and data collection points. CHW community health worker, T0 baseline (i.e., upon entry to the study after randomization but before participants receive the intervention), T1 immediate post intervention (3 months after T0, i.e., upon completion of the intervention), T2 3 months post intervention (6 months after T0, i.e., 3 months after completion of the intervention)

#### Fidelity of the intervention

The fidelity of the intervention will be ensured through the following means. First, at least one intervention conducted by each CHW will be randomly selected monthly to assess their compliance with the implementation protocol. Evaluations will be performed by the principal investigator. Second, the research team and the CHW will meet monthly to discuss the progress of the study.

The telephone follow-up and navigation assistance will be conducted 3 months following the multimedia education. The CHWs will make a monthly telephone follow-up to reinforce the knowledge of participants and motivate them to undergo cervical cancer screening. CHWs will also offer navigation assistance, including making a screening appointment, accompanying participants to undergo screening, and completing screening-related paperwork.

#### Control arm

Subjects in the control arm will be offered the CHW-led intervention after the outcome data of the participants in both arms are collected.

### Outcome measures

#### Primary outcome

The primary outcome is the cervical screening uptake. Participants will be asked whether they have ever had a Pap test. A receipt of the screening test should be shown to the research assistant who will record the dates when the screening tests were undertaken.

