## Hypothesis

Compared with the wait-list control arm, South Asian women in the intervention arm are expected to exhibit the following outcomes upon completion of the CHW-led multimedia intervention:higher rates of cervical screening uptake evidenced by a record/receipt of screening utilization;higher levels of readiness to undergo cervical cancer screening assessed by a question on readiness to undergo such screening; andhigher levels of perceived susceptibility to and seriousness of cervical cancer, perceived benefits of cancer screening, self-efficacy to undergo cancer screening, and lower levels in perceived barriers of cancer screening. (All items will be measured by the Cervical Cancer Screening Belief Scale.)

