## Methods

### Design

This project has two phases. Phase I aims to recruit and train six CHWs who will lead the intervention in Phase II. Phase II is a cluster randomized wait-list controlled trial that aims to implement and evaluate the effects of the intervention. The rationale of using a wait-list control is to allow an untreated comparison for the intervention arm to determine whether the intervention has an effect. In addition, it allows the wait-listed participants who have never had a Pap test and have not undertaken cancer screening in the past 5 years to have the opportunity to receive future interventions.

Standard Protocol Items: Recommendations for Intervention Trials (SPIRIT) 2013 (Additional file 1) will be used to report the study. The schedule for study enrollment, intervention, and outcome assessments is shown in Fig. 2 in the form of a SPIRIT diagram.

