##### Sociodemographics questionnaire

Age, ethnic group, monthly household income, years of formal education, marital status, employment status, number of years’ residence in Hong Kong, family history of cancer, and health insurance status of participants will be collected. Data on cues to action to screening (e.g., knowing where to go for screening) and any previous cervical screening experiences will also be collected.

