### Data collection

Data for the primary and secondary outcomes (except for the sociodemographics questionnaire) will be collected by a research assistant blinded to arm allocation at three time points: baseline (T0), i.e., upon entry to the study after randomization but before participants receive the intervention; immediate post intervention (T1, 3 months after T0), i.e., upon completion of the intervention; and 3 months post intervention (T2, 6 months after T0), i.e., 3 months after completion of the intervention. The research assistant will contact the participants in both arms to complete the questionnaire. All participants will receive HK$30 upon completing the questionnaire to promote their retention and complete the follow-up.

No data monitoring committee is involved in this study because the intervention is unlikely to introduce a risk or an adverse event to participants.

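### The primary outcome is worded as a lifetime question and no rule limits uptake to Pap tests dated after baseline, so pre-trial tests can count in either arm

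*Protocol article*

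**What the plan says.** All references are to the protocol article.

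- **Primary outcome.** The outcome is cervical screening uptake. The only question stated is "Participants will be asked whether they have ever had a Pap test". The next sentence adds: "A receipt of the screening test should be shown to the research assistant who will record the dates when the screening tests were undertaken". Which dates count is not said.
- **Subjects for Phase II.** A woman is eligible on screening history if she "never had a Pap test or has not undertaken cancer screening in the past 5 years". Someone last tested six years ago qualifies.
- **Design.** The rationale for the wait-list describes the wait-listed women as those "who have never had a Pap test and have not undertaken cancer screening in the past 5 years", with *and* in place of *or*.
- **Hypothesis.** The expectation is "higher rates of cervical screening uptake evidenced by a record/receipt of screening utilization".
- **Statistical analysis.** Effectiveness is judged by "comparing the proportions of subjects in both arms reporting cervical cancer screening uptake at T2". In the same sentence readiness is analysed as change from T0; uptake is not.
- **Data collection and Sociodemographics questionnaire.** The primary outcome is also collected at T0, and "any previous cervical screening experiences will also be collected".
- **Sample size.** The control rate of 37% is a survey figure for having ever had a Pap test. The intervention is expected to raise the rate to at least 60%.

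**The concern.** The intervention can only cause tests taken after it starts, but the stated question covers a woman's whole life. A participant whose last test was six years ago truthfully answers yes at T0, T1 and T2 in either arm. If her answer is what is counted, she is a success before the trial begins, and a new test does not change her classification.

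The word *ever* is not isolated: the sample size rests on a lifetime rate too. Nor does the analysis repair it, because the uptake comparison is made at T2 without reference to T0.

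Two analysts could follow this text on the same data and reach different primary results, one counting any test and the other only tests dated in the trial. If old tests were counted, the observed difference would be smaller than the true difference in new screening. With few clusters, it could also be shifted by chance imbalance in past testing.

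**Working it through.** **Inputs from the Sample size section:** 37% v 60%, 80% power, two-sided 5%, 72 per arm, 15% attrition, ICC 0.021, 68 women in each of six associations. **Assumed, because the protocol does not give it:** e, the share of women counted as screened through a pre-trial test, taken from 0 to 30%.

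**1. Reproduce the plan.** The two-proportion formula with pooled variance under the null uses p̄ = 0.485:

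n = [1.96 √(2 × 0.485 × 0.515) + 0.8416 √(0.37 × 0.63 + 0.60 × 0.40)]² / 0.23² = (1.385 + 0.579)² / 0.0529 = 72.9, so 73 per arm against the stated 72.

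Attrition: 72 / 0.85 = 84.7, so 85 per arm, as stated. Solving 2 × 85 × [1 + (m − 1) × 0.021] = 6m gives m = 68.5 against the stated 68. With 68 per association the design effect is 1 + 67 × 0.021 = 2.407. The effective number per arm is then 204 × 0.85 / 2.407 = 72.0. Power at 72 per arm is 0.795. The planned figures reproduce closely.

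**2. Effect of counting pre-trial tests.** With new-uptake rate p, the observed rate is e + (1 − e)p, so the amount added is e(1 − p). This is larger in the arm with the lower rate, which is why the difference shrinks:

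observed difference = (1 − e)(p_T − p_C)

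Example at e = 0.20: control 0.20 + 0.80 × 0.37 = 0.496 (12.6 points added), intervention 0.20 + 0.80 × 0.60 = 0.680 (8.0 points added), difference 18.4 points.

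Taking 37% and 60% as the new-uptake rates, with 72 effective women per arm:

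| e | Control | Intervention | Difference (points) | Power |
|---|---|---|---|---|
| 0 | 37.0% | 60.0% | 23.0 | 0.795 |
| 10% | 43.3% | 64.0% | 20.7 | 0.706 |
| 20% | 49.6% | 68.0% | 18.4 | 0.613 |
| 30% | 55.9% | 72.0% | 16.1 | 0.521 |

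The summed binomial variance hardly moves: 0.473, 0.476, 0.468 and 0.448 down the rows. The loss of power comes from the smaller difference.

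**3. Dependence on the true rates.** If new uptake were 10% v 33% (assumed), power on the same basis would be 0.927, 0.785, 0.629 and 0.493. The starting level differs, but the decline remains.

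**4. Unequal shares.** Let the share be e_T in the intervention arm and e_C in the control arm. At 37% v 60%:

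- e_T = 0.20, e_C = 0.10: 68.0% − 43.3% = 24.7 points.
- e_T = 0.10, e_C = 0.20: 64.0% − 49.6% = 14.4 points.

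With no true effect (37% in both arms), e_T = 0.20 and e_C = 0.10 give 49.6% − 43.3% = 6.3 points from past testing alone.

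**5. Plausible size of e before any receipt rule.** Suppose 37% of the source population were ever tested and a fraction r of those were last tested more than 5 years ago. The share among eligible women is then 0.37r / (0.63 + 0.37r): 5.5% at r = 0.10, 12.8% at r = 0.25 and 22.7% at r = 0.50. The value of r is an assumption. A strict receipt rule would lower e further.

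**The case against.** The strongest reply is that the design already collects what is needed to separate old tests from new ones. The lifetime question is an interview item; the next sentence asks for a receipt and records the date of each test. Uptake is measured at T0, previous screening is recorded, and the Objectives section places the effect after the intervention. An analysis plan that is not shown may turn these dates into a post-baseline outcome. Few women may still hold a receipt more than 5 years old, and dilution would usually pull towards no effect.

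Most of this stands, and it rules out several stronger readings that a reader might infer:

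- *That the plan counts pre-trial tests.* No section says so. The wording permits it.
- *That a new test in a previously tested woman cannot be seen.* It can, because test dates are recorded. What is missing is a rule that uses them.
- *That self-report will replace the receipt.* The word *reporting* in the Statistical analysis section invites this. But the Hypothesis, Primary outcome and Discussion sections all rest on a receipt or record, so it is best read as loose wording.
- *That it is unsettled whether previously tested women are enrolled.* The Design sentence is a rationale for the wait-list. The inclusion criterion governs, and the Discussion's description of the target women as rarely or never screened agrees with it.
- *That power falls from 86% to 65%, 48% or 36%.* Those figures need an assumed new uptake of 5% v 28%, an assumed e and a cluster-level t test on 4 degrees of freedom. The plan uses a permutation test over the six associations.

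The reply does not remove the core point. The article does state the primary question and the primary comparison, and neither is tied to a date. The receipt *should* be shown, but the text does not say that a yes without a receipt counts as a no.

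**Conclusion.** The concern holds as a defect in how the primary outcome is fixed: a lifetime question, an eligibility rule that admits women tested more than 5 years ago, and a T2 comparison with neither a post-baseline window nor use of T0. On the literal wording a pre-trial test can count as uptake in either arm.

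The size is conditional. For e between 10% and 30%, the 23-point difference shrinks by 2.3 to 6.9 points, and power drops by about 9 to 27 percentage points from about 80%. This assumes equal e in both arms, 37% v 60% as the new-uptake rates and the protocol's two-proportion basis; it is not the power of the planned permutation test. The documents do not give e, and it could be close to zero under a strict receipt rule. With unequal shares across three associations per arm, the error could go in either direction.

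**What to change.** - **Primary outcome:** define it as a receipt- or record-verified Pap test dated after T0 and up to T2 (6 months after T0), with the same window in both arms. Remove *ever had* from the definition; previous testing is already covered by the baseline questionnaire. State how a claimed test without a receipt or record is counted.
- **Statistical analysis:** replace *reporting* with wording that refers to this verified, dated outcome. Self-reported new tests could be given as a sensitivity analysis.
- **Design:** align the *and* in the wait-list rationale with the *or* of the inclusion criterion.
- **Sample size:** note that 37% is a lifetime rate from a survey and not the expected 6-month rate of new screening in the enrolled women.

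The cost is wording and that note. Receipts and test dates are already to be collected, so no new data are needed.
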